### Statistical methods

#### Clinical outcomes analysis

The primary outcome will be analysed on intention-to-treat at the 6-month time point (prior to progressing to further condition-specific care). The average reduction in PAC-QOL score will be analysed using linear mixed-model regression with a random effect for centre and fixed effects for intervention, gender, baseline PAC-QOL and breakthrough medication.

Secondary outcomes will be analysed at 6-months and at additional time points (3 and 12 months from end of treatment) including the percentage of patients achieving a 1-point reduction. Outcomes will take the form of count (change in number of symptom episodes), ordinal (patient’s global impression of success) and continuous (questionnaire scores) data. Regression models, with a random effect for centre, appropriate to the outcome data types will be fitted to estimate the treatment effect, adjusting for baseline values (when appropriate), gender, and breakthrough medication use as a potential confounder.

Predictive modelling using baseline characteristics: measures of chronic pain, autonomic symptoms, joint hypermobility, cognitive, behavioural and mood variables share the common hypothesis that they are detrimental to the success of all treatments, i.e. they perpetuate illness in spite of therapy. Appropriate regression models will be developed to determine the influence of these pretreatment characteristics on the success of treatments.

Analysis will be performed using proprietary software (Stata, Stata Corp., College Station, TX, USA) by the appointed study statistician. *P* < 0.05 will be taken to indicate statistical significance. No analyses will be conducted until a statistical analysis plan (SAP) has been written and reviewed by an independent statistician. The SAP will be approved by the senior statistician and chief investigator. Multiple imputation will be used to address missing values. Subgroup analyses will be performed for selected baseline characteristics.

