#### Group 1: habit training (HT)

Habit training will be provided by trained specialists (e.g. nurses or physiotherapists) with clinical experience, who have undertaken an additional study-specific standard 1-day training session. A standardised approach and intervention will be provided via use of an intervention manual; at least one random observation visit will be performed early in the study by lead research nurses for quality control.

The course of therapy will include a minimum of three, maximum of four sessions (45–60 min each session). This will use a standardised session proforma with an interval tolerance of every 3–5 weeks. The first and last session will always be face to face. Sessions will be delivered by the same therapist if at all possible and tailored to participants’ individual needs. Each recruiting site will provide sufficient resource to cover visits in therapist absence or holiday. Participants will receive the interventions in Table 1 which are covered in a booklet given to each participant. The therapist is prohibited from using digital rectal examination to train manoeuvres and will complete relevant sections in the participant booklet advising on individual instructions.

**Table 1 Tab1:** Interventions for habit training (HT – group 1)

a. Provision of a written information leaflet covering normal bowel function; causes of constipation; diet and fluid advice; getting into a good bowel habit
b. Review of written information using locally available teaching tools such as models or diagrams
c. Advice to stop all laxatives including drugs which have a laxative effect or over the counter herbal teas that contain strong purgatives. One or two glycerin suppositories are permitted as rescue if no stool is passed for 3 days. No use of irrigation devices or enemas
d. Encouragement to follow a daily routine: sit on the toilet for 20–30 min after first meal and/or hot drinks (sooner if urge felt)
e. Advice to attempt defaecation after meals or when urge is felt, but no more than 3 times per day
f. Advice to sit on toilet with knees bent to 45° position with feet elevated on stool or equivalent; abdominal brace and breathe while performing anal relaxation
g. Advice only to attempt to push for 5–10 min maximum
h. Teaching on defaecation manoeuvres, taught while the patient is positioned sitting on chair with verbal coaching to breathe while pushing
i. Strong discouragement from multiple attempts and prolonged straining

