#### Laxative use

All participants will be asked to discontinue laxative use at the first intervention visit and to refrain from using laxatives throughout the trial, as is standard UK practice in specialist biofeedback services. However, it is inevitable that participants will seek recourse to laxatives and other dietary supplements during the course of the programme. Experience shows that complete prohibition can lead to unreported laxative use, which might confound findings. Although we will strongly discourage ad libitum medication usage and specify a defined breakthrough regimen, we will record co-treatment with sufficient fidelity and integrity to enable use as covariates in analyses using a specific journal for this purpose (within the patient journal: see ‘Study Outcome Measures’). A concomitant medications list, including a shortlist of contributory or confounding medications, will be used to filter on data entry.

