##### Visit 1: screening, consent and baseline assessments

Visit 1 will be conducted face-to-face in clinic. Following a detailed discussion about the trial, eligible and agreeable patients will complete written informed consent. Screening and confirmation of eligibility will be followed by standardised medical and surgical history by interview including previous medication usage. Clinical examination findings (carried forward if performed previously within last 3 months) and standardised examination of the perineum/anus/rectum/vagina will be performed.

Baseline assessments include several key validated assessments that profile patients for important characteristics informing disease pathophysiology and important potential predictors of treatment response. This includes the constipation and irritable bowel syndrome modules of the Rome III questionnaire [70], the Cleveland Clinic Constipation Score Questionnaire [71], brief chronic pain, autonomic symptoms [72] and joint hypermobility [73] assessments and St. Mark’s Faecal Incontinence Score [74]. All were selected on the basis of trade-off between adequate detail and brevity. These instruments have been collated into a single booklet with design and presentation optimised by patient representatives. Participants will complete the questionnaire booklet (containing baseline, primary and secondary outcomes listed above), and be given a baseline 2-week patient diary and journal. All participants will be asked to complete the 2-week patient diary prior to INVEST, HT or HTBF interventions and prior to stopping laxatives.

Urinary pregnancy testing will be made available to women of child-bearing potential at eligibility assessment and advice will be given to all women regarding the need to prevent pregnancy during the study intervention period. Randomisation to HT-, HTBF- or INVEST-guided intervention will be completed at the end of visit 1.

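### The primary and secondary clinical models adjust for breakthrough medication, a post-randomisation variable, so their treatment coefficient is generally not the intention-to-treat effect if allocation affects its use

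*Protocol article*

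**What the plan says.** In the protocol article, Clinical outcomes analysis, the main analysis is described thus: "The primary outcome will be analysed on intention-to-treat at the 6-month time point". The model is a linear mixed regression with a random effect for centre and "fixed effects for intervention, gender, baseline PAC-QOL and breakthrough medication". The secondary clinical outcomes get regressions suited to their data type, "adjusting for baseline values (when appropriate), gender, and breakthrough medication use as a potential confounder". The qualifier about appropriateness attaches only to the baseline values. No model without breakthrough medication is given.

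The timing comes from other sections:
- Visit 1: "Randomisation to HT-, HTBF- or INVEST-guided intervention will be completed at the end of visit 1".
- Laxative use: "All participants will be asked to discontinue laxative use at the first intervention visit". A breakthrough regimen applies from then on, and the stated purpose of recording is explicit: "we will record co-treatment with sufficient fidelity and integrity to enable use as covariates in analyses".
- Table 1, item c (habit training, which the HTBF sessions also include in full): "One or two glycerin suppositories are permitted as rescue if no stool is passed for 3 days".
- Visits 2–5 and Visits 6–8: changes in confounding medications are reviewed at each intervention visit and again at follow-up.

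**The concern.** A confounder of a randomised comparison would have to influence allocation, or share a cause with it. Something that happens after allocation can do neither. Breakthrough use starts once laxatives have been stopped at the first intervention visit, and the permitted rescue follows three days without a stool, which is the kind of symptom both therapies aim to relieve. If one strategy works better, its participants may well need less rescue.

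Putting such a variable in the model does two things. It removes whatever part of the effect runs through the changed need for medication. It also links the arms to unmeasured severity: among participants with the same rescue use, the arms no longer have the same severity mix if severity drives both rescue and PAC-QOL. At stake is the coefficient that will be reported as the answer to both randomised questions, and the matching coefficients for the secondary clinical outcomes.

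**Working it through.** **1. Is the variable post-randomisation?** Randomisation closes visit 1. Laxatives stop at the first intervention visit, which comes later. Breakthrough use presupposes that stop, so it cannot be a baseline measurement.

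**2. The plan's own target.** Sample size section: difference 0.4, SD 1, 90% power, 5% significance (two-sided).
- n per arm = 2 × (1.960 + 1.282)² / 0.4² = 2 × 10.51 / 0.16 = 131.4, so 132.
- With 10% loss: 132 / 0.9 = 146.7, so 147; 90 / 0.9 = 100; 2 × 147 + 100 = 394.

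These agree with the protocol. The calculation is for a difference of 0.4 between arms, with no conditioning on anything after randomisation.

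**3. What the adjusted coefficient estimates.** The document gives no rescue rates and no association of rescue with outcome, so everything in this step is assumed. Let A be arm (1 = better arm), U unmeasured severity (mean 0, SD 1), M any breakthrough use, and Y the PAC-QOL reduction:
- logit P(M = 1) = U − gA, which gives 50% use in the comparator arm; g is set so that use is lower by d in the better arm.
- Y = direct × A + b × M − s × U + error, with the direct effect chosen so that the total effect is 0.40.

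Regression on A alone returns 0.40. Regression on A and M returns, in large samples,

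adjusted = total + d × (b − k × s), where k = average within-arm Cov(U, M) / average within-arm Var(M).

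For d = 0.20 (use 50% and 30%): average variance = (0.25 + 0.21) / 2 = 0.230; average covariance by numerical integration = (0.207 + 0.177) / 2 = 0.192; k = 0.192 / 0.230 = 0.83. For d = 0.10: 0.203 / 0.245 = 0.83.

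**4. Numbers** (b = effect on PAC-QOL reduction that goes with use at given severity; s = points per SD of severity):

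| d | b | s | adjusted estimate |
|---|---|---|---|
| 0 | any | any | 0.40 |
| 0.20 | −0.5 | 0.5 | 0.40 + 0.20 × (−0.5 − 0.417) = 0.22 |
| 0.20 | −0.3 | 0.3 | 0.40 + 0.20 × (−0.3 − 0.250) = 0.29 |
| 0.20 | 0 | 0.5 | 0.40 + 0.20 × (−0.417) = 0.32 |
| 0.20 | 0 | 0 | 0.40 |
| 0.20 | +0.3 | 0.5 | 0.40 + 0.20 × (0.3 − 0.417) = 0.38 |
| 0.20 | +0.5 | 0 | 0.40 + 0.20 × 0.5 = 0.50 |
| 0.10 | −0.5 | 0.5 | 0.40 + 0.10 × (−0.5 − 0.414) = 0.31 |
| 0.10 | +0.5 | 0 | 0.40 + 0.10 × 0.5 = 0.45 |

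The row with b = 0 and s = 0.5 is collider bias alone: rescue does nothing to the outcome, yet the estimate moves by 0.08.

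**5. True null.** The shift d × (b − k × s) does not contain the total effect. With a true effect of zero the adjusted estimate would therefore run from −0.18 to +0.10 at a 20-point difference in use, and from −0.09 to +0.05 at 10 points.

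**The case against.** The best defence is that the investigators meant this. The Laxative use section expects participants to turn to laxatives and wants co-treatment accounted for, so that it does not blur the comparison. That is a legitimate question, but it is a different one: the effect had breakthrough use been the same in both arms. The protocol does not state that estimand, and entering observed use as a covariate does not identify it when unmeasured severity drives both use and outcome. The label the protocol gives, "breakthrough medication use as a potential confounder", is not that rationale either.

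Several stronger readings are tempting, and the document does not support them:
- **That the estimate is biased outright.** It is not if allocation leaves breakthrough use unchanged. All arms get the same advice to stop laxatives, and no rates by arm are given.
- **That adjustment always pulls the effect towards or past zero.** This follows only if users are assumed to do worse, or if severity dominates. If rescue relieves symptoms and props up the weaker arm, the estimate can stay near 0.40 or rise to 0.50. A negative b treats use as lowering the outcome in itself; at best it is a rough stand-in for use marking a poor interim response.
- **That power falls to some particular low figure.** Any such figure comes from one corner of an assumed grid.
- **That breakthrough use is simply treatment failure.** The three-day trigger covers only the permitted suppositories. The protocol also foresees ad libitum laxatives and supplements, which may reflect habit as much as non-response.
- **That the intention-to-treat population is abandoned.** Participants are kept and followed whatever happens to their treatment. The fault lies in what the coefficient estimates.
- **That every model in the trial is affected.** The predictive models use baseline characteristics, and the economic analysis refers only to trial covariates.

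None of these limits removes the defect: the reading of the primary result would rest on a condition that nobody can check in advance.

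**Conclusion.** The point holds in its conditional form. The protocol article fixes a post-randomisation variable, wrongly described as a potential confounder, in the primary model and in the secondary clinical regressions. If allocation affects breakthrough use, the treatment coefficient is in general not the total randomised effect for HTBF v HT or INVEST v No-INVEST; the components can cancel, but only by chance. If use is the same in all arms, nothing is lost.

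The size is unknown. Against a target of 0.40, the assumed scenarios give shifts of −0.18 to +0.10 at a 20-point difference in use and −0.09 to +0.05 at 10 points. They rest on a linear model without interaction, 50% use in the comparator arm, an effect of use between −0.5 and +0.5 points, and severity between 0 and 0.5 points per SD. They show that the shift can matter; they do not predict it. They were worked for two equal arms. The same mechanism applies to INVEST v No-INVEST, but that comparison was not computed separately.

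This is not a detail left to the analysis plan: the covariate list is stated, and it should be changed before any outcome is analysed.

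**What to change.** - Delete breakthrough medication from the fixed effects of the primary model and of the secondary clinical outcome regressions. Keep intervention, gender, the baseline value (where there is one) and the random effect for centre. Amend the sentence in Laxative use that earmarks co-treatment as a covariate.
- Report breakthrough use by randomised arm as an outcome.
- If adjustment for laxative habit is wanted, use only what is recorded before randomisation, such as the medication history taken by interview at visit 1. The baseline diary is handed out at visit 1 and covers the following two weeks, while randomisation closes that visit, so the diary is kept after allocation.
- Keep any model that accounts for breakthrough use as a labelled supportive analysis, with its estimand and its assumptions about unmeasured severity stated.
- The baseline predictive models need no change.

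The cost is a few lines of wording in the protocol and analysis plan. Data collection and the total of 394 are unchanged. With the covariate removed, the model estimates the total effect for which 132 per arm was calculated.

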#### Health economic outcome analysis

The pragmatic multicentre trial design reflects real-world clinical practice, thus cost and outcome profiles are likely to reflect routine care in NHS settings. Individual patient data collected within the trial included NHS treatment and personal costs as well as health status estimated as quality-adjusted life years (QALYs). Cost-effectiveness analysis will capture the effect of treatment as changes in cost and QALYs. The base case analysis will proceed using multiple imputation of patient data to manage missing values, following good practice guidance [78, 79]. Imputed datasets will be analysed independently and the estimates obtained will be pooled to generate mean and variance estimates of costs and QALYs using Rubin’s rule [75]. Each analysis will use a bivariate regression modelling approach to capture the correlation of costs and outcomes as well as covariates within each model. Models will be bootstrapped with 5000 replicates, using Stata. Supportive sensitivity analyses, including complete case analysis, will be used to explore the impact of imputation and missing data.

Cost-effectiveness models that extrapolate beyond 3–6 months’ duration are problematic in adult constipation, as outcomes are contingent upon subsequent care received and the underlying disease process. However, the programme of work packages provides a unique opportunity to construct probabilistic models exploring optimal pathways from effectiveness and cost-effectiveness perspectives. Since patients will (within the CapaCiTY programme) be followed along a pathway that includes a series of steps of care, it will be possible to construct costs and outcomes for a range of patient pathways providing comparative longer-term cost-effectiveness estimates. For example, it will be possible to ask whether INVEST or No-INVEST-led first-line care leads to lower overall costs or improved outcomes. For the overall CapaCiTY programme of studies, patient-level data from recruitment through the various work packages will be used to construct pragmatic, probabilistic models to explore optimal pathways from effectiveness and cost-effectiveness perspectives.

Since EQ-5D and EQ-VAS typically have SDs of 30% of scale: a 10% difference deemed clinically significant can be detected with the large sample sizes proposed within the trial. Adjustment for time preference will be at the socially accepted rate for cost-effectiveness analyses (currently 3.5% for costs and benefits). Patient use of resources and EQ-5D values will be used to estimate the cost-effectiveness of the three comparisons being studied. A base case analysis will estimate within trial incremental cost/quality-adjusted life years (QALYs) gained from an NHS perspective, with missing values imputed and with adjustment for trial covariates. A range of supportive sensitivity analyses will include a complete case analysis, effect of covariate adjustment and analysis perspective.

#### Nested qualitative study: patient and health professional experience

Face-to-face, semistructured interviews will be conducted involving a diverse sample of patients and professionals purposefully selected at various time points throughout the study:Before starting to gauge expectationsDuring treatment to explore fidelity and ease of adherenceImmediately after, and up to 2 years after, intervention, to explore perspectives on the intervention and longevity of any benefit and pattern of response over time

Participants for interview will be selected from a sampling grid of potential interviewees from all three arms, both improved and not improved by intervention, to reflect a range of ages, geographical locations and, where possible, other pertinent attributes such as ethnicity and gender. Approximately 50 interviews (or until apparent data saturation) will be conducted with participants. We will also interview 10 professionals delivering the intervention, to determine comparative ease of delivery of the two interventions.

Separate informed consent will be taken for interviews (see Additional file 2 for Consent Form). Interviews will be conducted throughout to capture relatively early and later experiences and perceptions of the interventions. A topic guide for the interviews, informed by the existing literature and our patient advisors, has been developed.

#### Qualitative analysis

Interviews will be digitally recorded, anonymised, transcribed verbatim and analysed using a pragmatic thematic analysis and NVivo8 software (QSR International Ltd., Warrington, UK) for data management. Data analysis will be developed as outlined by Fereday and Muir-Cochrane [78] in the first instance by mapping key concepts derived from the transcripts (‘charting’) and extracting emergent themes from the transcripts. A second researcher will conduct independent analyses and then compare and refine resulting codes and themes in discussion. Emergent themes, together with captured observational data, will form the basis of analytical interpretation.

### Monitoring and audit

The PCTU quality assurance manager will conduct a study risk assessment in collaboration with the CI. Based on the risk assessment, an appropriate study monitoring and auditing plan will be produced according to PCTU SOPs. This monitoring plan will be discussed and authorised by the sponsor before implementation. Any changes to the monitoring plan must be agreed by the PCTU quality assurance manager and the sponsor. Audits may be conducted by the sponsor or funder representative. The study may be identified for audit via the risk assessment process, investigator or department request, allegation of research misconduct or fraud or a suspected breach of regulations or selected at random.

### Trial committees

The trial and the whole CapaCiTY programme will be overseen by a Programme Steering Committee (PSC). The role of the PSC is to provide overall supervision of the study on behalf of the sponsor and funder to ensure that the study is conducted in accordance with the principles of GCP and relevant regulations.

The responsibilities of the PSC will include: ensuring that views of users and carers are taken into consideration; advising on the trial protocol; advising on changes in the protocol based on considerations of feasibility and practicability; assisting in resolving problems brought to it by the Programme Management Group (PMG); monitoring the progress of the trial and adherence to protocol and milestones; considering new information of relevance from other sources; considering and acting on the recommendations of the Data Monitoring and Ethics Committee (DMEC), sponsor and/or Research Ethics Committee (REC); reviewing trial reports and papers for publication.

The PMG will meet monthly initially during study set-up and then every 2 months. The PMG will be responsible for day-to-day project delivery across participating centres, and will report to the PSC.

The DMEC will meet at least 4 weeks prior to the PSC to enable recommendations to be fed forward. The DMEC will comprise an independent chair an independent statistician and a clinician.

A Constipation Research Advisory Group (CRAG) will comprise eight patients and two lay members. This group will have geographical diversity and a disease-appropriate demographic (eight women, two men). The CRAG will be involved in review of participant information sheets, booklets, diaries and advertising/marketing materials, project management by representation on the PSC, parallel qualitative analysis, dissemination of results and lay summaries, and presentations at local research events.

There are no plans for interim analysis as this is a low-risk study.

